### Analysis

To address the primary aim of this study, we will conduct three main tests. To assess the impact of the intervention, we will perform an analysis of covariance (ANCOVA) on the post-intervention (12-week) physical activity levels of the participants in the two conditions, with their baseline scores as a covariate [53]. To determine the sustainability of the physical activity levels at 6 and 12 months, we will perform two ANCOVA on post-intervention (6 and 12 months, respectively) physical activity levels of the participants in the two conditions, with baseline scores as covariates.

To examine the data on the first of the secondary aims (determining the effect of the clinician referral and the physical activity program on psychological well-being, quality of life, and objective physical functioning) we will use the same analytical strategies as for the primary aim (ANCOVA with baseline scores as a covariates [53]). For this analysis, the dependent variables will be the subscales of the quality of life, anxiety, and depression measures, as well as the separate measures of objective physical functioning. The immediate effects of the intervention will be assessed using the 12-week data. The sustainability of the effects of the intervention on quality of life, anxiety, and depression will be assessed at 6 and 12 months.

To address the final aim, we will use path analyses to test for possible mediation of the intervention effect on level of physical activity based on the Baron and Kenny [54] approach. We will only test the components of SCT as possible mediators if they were affected by the intervention (i.e., group assignment) and associated with follow-up participation in physical activity. This approach requires that the outcome (i.e., participation in physical activity) be regressed on the proposed mediators (i.e. SCT components) and the intervention (i.e., group assignment coded as "0"= control and "1"= intervention). Mediation is present when the proposed mediator maintains a significant relationship with the outcome whereas group assignment does not. For the path analysis, we will adjust for the same variables as in the main analyses.

For all analyses, we will employ the intention-to-treat principle for all participants with available data at post intervention and follow-up.

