## Discussion

To the best of the authors' knowledge, this trial is the first to consider the efficacy of clinician referrals to a physical activity program to increase physical activity levels among cancer survivors. Although there is an expanding evidence that provides strong support for promoting physical activity among survivors of prostate cancer [5], substantial work has yet to be undertaken on how this research could be implemented into clinical practice.

This trial also has a strong emphasis on behaviour change and the mechanisms through which this change occurs. This addresses a limitation of previous research, as few randomised controlled trials of cancer survivors, or indeed other population groups, have examined the effects of a physical activity intervention on potential mediators of behaviour change and physical activity adherence using a theoretical model. In applying social cognitive theory, the intervention design addresses key constructs in social cognitive theory and examines if these factors change as a result of the intervention and if this change, in turn, explains change in physical activity participation. This investigation provides data that will assist in the design of physical activity trials that have behaviour change as a primary aim and outcome.

In the present study, we investigate one way in which the physical activity levels of prostate cancer survivors could be increased, to improve health outcomes while incorporating social and cognitive mechanisms that may contribute to desired outcomes. Findings from this research may have implications for the treatment of not only prostate cancer survivors but also other cancer survivors and those with other chronic health conditions.

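### The path analysis adjusts only for baseline activity, so baseline health or mood that affects both the social cognitive components and later activity can bias the mediator coefficient and be read as mediation

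*Protocol article*

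**What the plan says.** The Analysis section bases the mediation test on the Baron and Kenny approach. On the model: "This approach requires that the outcome (i.e., participation in physical activity) be regressed on the proposed mediators (i.e. SCT components) and the intervention". On covariates: "For the path analysis, we will adjust for the same variables as in the main analyses". The main analysis at 12 weeks is an ANCOVA on "physical activity levels of the participants in the two conditions, with their baseline scores as a covariate", and those at 6 and 12 months likewise use baseline scores only. The covariate set of the path analysis is therefore fixed by cross-reference as baseline activity.

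A component is tested as a mediator only if group assignment affected it and it is associated with follow-up activity. The decision rule is then: "Mediation is present when the proposed mediator maintains a significant relationship with the outcome whereas group assignment does not".

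Under Design, it is clinicians who are randomised to a condition. Under Procedures, all measures are collected at baseline in both conditions. These include the EORTC questionnaires, MAX-PC, CES-D, the functional tests and the social cognitive components themselves. The Discussion presents the mediation work as a strength, in that the trial "examines if these factors change as a result of the intervention and if this change, in turn, explains change in physical activity participation".

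**The concern.** Randomisation protects the effect of group on the mediator and the effect of group on activity. It does not protect the association between mediator and activity within arms, which is the other half of any mediation claim. A man in better health or mood may be both more confident about exercising and more active later, without the confidence causing the activity.

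The protocol makes this plausible. Its Background reports pilot work in which low confidence after treatment, other illness and loss of function with age all emerged as obstacles to activity. Baseline activity stands in for such factors only in part.

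At stake is the further aim on mechanism, which is meant to inform the design of later trials. The entry conditions help only partly. The protocol hypothesises that the intervention shifts every component, and confounding alone can satisfy the condition that the component be associated with activity.

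**Working it through.** The protocol gives no sample size, power or expected effect for the mediation analysis, so there is no figure to reproduce. The check is a model with a true mediator effect of zero.

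**Inputs from the protocol (Participants).** 220 recruited with 10% attrition: 220 × 0.9 = 198 analysed. Effect size d = 0.484. α = .05, taken as two-sided.

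**Assumed inputs.** Baseline activity P correlates .5 with follow-up activity. One baseline factor U (health or mood) has path a to both mediator and activity, with a = .2, .3 or .4. Clustering is not modelled.

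**Model.** Within-arm variances are 1.
- M = δ·group + a·U + √(1 − a²)·e₁
- Y = c·group + .5·P + √.75·(a·U + √(1 − a²)·e₂)
- Setting A: δ = .4, c = .484.
- Setting B: δ = .5, c = .75 × .484 = .363.

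**Step 1, bias with the planned adjustment (group and P), U unrelated to P.** The expected mediator coefficient is √.75·a², where the truth is 0:
- .866 × .04 = .035
- .866 × .09 = .078
- .866 × .16 = .139

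**Step 2, false significance of the mediator.** The partial correlation of M and Y is r = a². With 198 − 4 = 194 residual degrees of freedom, the noncentrality is r/√(1 − r²) × √194 = 0.56, 1.26 and 2.26. A two-sided 5% test then rejects in about 9%, 24% and 61% of trials. Simulation gives about 8%, 23% and 63%, the same within simulation error.

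**Step 3, U correlated .5 with baseline activity.** The coefficient becomes √.75·a²·(1 − .25)/(1 − .25a²). For a = .4 this is .139 × .75/.96 = .108, about a fifth to a quarter less than in step 1. The mediator is falsely significant in about 6%, 17% and 42%.

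**Step 4, the protocol's full rule.** This requires group to shift the component, total effect and mediator both significant, and group not significant once the mediator is in the model. Simulated rates with U unrelated to P:

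| Path a | Mediator significant | Full rule, setting A | Full rule, setting B |
|---|---|---|---|
| .2 | about 8% | about 0.5% | about 2% |
| .3 | about 23% | about 1% | about 5% |
| .4 | about 63% | about 3% | about 14% |

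In a variant of setting B with the path from U to activity set at a full a SD, and U's correlation with baseline activity between 0 and .5, the full rule was met in 1% to 19%. Group-to-mediator and mediator-to-activity were both significant in 8% to 72%.

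**Step 5, spurious indirect effect in setting A.** δ × bias = .4 × .035, .4 × .078 and .4 × .139 = .014, .031 and .055 SD. That is about 3%, 6% and 11% of .484.

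**Step 6, U added as a covariate.** The coefficient returns to about 0 and false significance to about 5%. In the variant of step 4, the full rule is then met in 0.7% or fewer.

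**Step 7, the intervention does not shift the component (δ = 0).** In that variant the two paths are both significant in 4% or fewer, so confounding turns into false mediation mainly for components that the intervention moves.

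**The case against.** The strongest reply is that false significance of the mediator is not what the protocol calls mediation. A reader might infer from the 63% figure that confounding will be declared as mediation in most trials. The documents do not support that. The decision rule also requires group to lose significance, and in setting A this holds false mediation to about 3% even at the strongest path. This part of the reply stands, and the point is therefore that confounding can be read as mediation, not that it will be.

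It also stands that the confounder strengths are assumed, that at .2 the inflation is small, and that health which drives exercise should have left its mark on baseline activity, which is adjusted for. Step 3 shows that this last argument reduces the bias without removing it.

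A reader might further infer that the lack of a sensitivity analysis for unmeasured confounding is a defect. It is not a finding here, because an article may leave that to the analysis plan. The covariate sentence is different: the article fixes the set, so this is not a detail left open.

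The strict rule does not answer the concern altogether. The mediator coefficient is biased upward whichever rule is applied. Readers will also see the two significant paths, which arise falsely much more often than the full rule is met.

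**Conclusion.** The point holds in a limited form. The covariate set of the path analysis was taken over from a randomised comparison and does not fit the unrandomised mediator-to-activity step, although relevant baseline measures are in hand. Under assumed paths of .2 to .4 SD and no true effect, the mediator coefficient is biased upward by about 0.03 to 0.14 SD and is falsely significant in about 8% to 63% of trials, or 6% to 42% if the confounder correlates .5 with baseline activity. The full rule is falsely met in about 0.5% to 3% in setting A, and in up to about 14% to 19% with a smaller direct effect and larger mediator shift.

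These figures show sensitivity to assumed strengths, not an expected bias. They assume a single, perfectly measured confounder, 198 men and no clustering. A reader might take the point to weaken the trial's main result. It does not, because the primary and secondary ANCOVAs compare randomised groups. It is a cheap improvement to the further aim.

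**What to change.** In the regression of activity on mediator and group, replace the reference to the main-analysis variables with a pre-specified set:
- baseline activity;
- the baseline score of the mediator under test;
- baseline global quality of life (EORTC QLQ-C30), CES-D, MAX-PC and 6-minute walk.

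All of these are collected at baseline in both conditions. Hormone treatment appears only in the eligibility criteria and not among the listed measures, so the fix does not depend on it. State the mediation conclusion as conditional on no unmeasured confounding of the mediator-to-activity path.

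The cost is five further covariates, each entered as one score, which takes the residual degrees of freedom from 194 to 189. No new data are needed. Confounding that these scales miss or measure imperfectly will remain, so the return to 5% in the calculation is a best case.

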### Study aims and hypotheses

The primary aim of the ENGAGE study is to compare the efficacy of a clinician referral and 12-week, supervised, exercise physiologist-led physical activity program compared to usual care (no referral to the physical activity program and typically minimal advice about physical activity) in improving the physical activity levels of prostate cancer survivors at three post-intervention time points:12 weeks, 6 months, 12 months. We hypothesise that participants in the intervention condition will be more physically active than participants in the control condition.

A secondary aim is to determine the effects of the clinician referral and physical activity program on the psychological well-being, quality of life and objective physical functioning of prostate cancer survivors. At the three post-intervention time points (12 weeks, 6 months, 12 months), we hypothesise that the clinician referral and physical activity program will improve participants' quality of life and decrease anxiety and depressive symptoms over and above changes on such measures that participants in the control condition may experience at post intervention. We will measure objective physical functioning at baseline and 12 weeks only, and hypothesise that participants in the intervention condition will improve their exercise capacity more than those in the control condition.

A further aim is to assess the impact of the intervention on main health determinants using the social cognitive theory and whether these determinants mediate behaviour change. We hypothesise that the intervention will have positive effects on self-efficacy, outcome expectations, goals, and socio-structural factors; and that self-efficacy will have a direct association with physical activity and an indirect association, mediated by outcome expectations, goals, and socio-structural factors.

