### Participants

Eligible patients will be adult males who 1) have completed active treatment for prostate cancer within the previous three-12 months. Participants currently on hormone treatment will be eligible to participate; 2) were treated with curative intent, representing stages I, II, or III; and (3) have the ability to complete surveys in the English language. Patients will be excluded from this study if they have musculoskeletal, cardiovascular, or neurological disorders that could limit them from exercising. The patients' treating clinicians will assess their eligibility for the study.

The sample size for this study was calculated based on the primary research question; number of minutes of moderate or strenuous physical activity in a typical week in past month as measured by an adapted version of the Leisure Time Exercise Questionnaire at the completion of the 12 week intervention using the following assumptions: (1) a medium-sized effect will be found, (2) α will be set at .05, (3) power will be set at .80, (4) the attrition rate will be 10% at 12 weeks, and (5) the design effect will be 1.084. The anticipated effect size was judged from a similar project [24], where a medium-sized effect was found for the outcome of a physical activity intervention (*d *= 0.484), where the intervention group increase their total weekly minutes of physical activity by 59.3 minutes (SD = 126.6).

Physical activity levels will be measured at 12 weeks to answer the primary research question. An attrition rate of 10% is expected, based on our previous work in this area [22]. A design effect of 1.084 was included to account for clustering (ICC = .005, *m¯¬ *= 16.83). The ICC was estimated from a recently completed study investigating recruitment of newly diagnosed prostate and colorectal cancer patients (clustered by specialist) [22] and from published commentary in which the authors suggested that ICC rates of less than 0.01 have been found for practitioner prescribing rates [23]. The average size of each cluster (*m¯*) was calculated from an estimation of the number of participants needed in this study before the application of the design effect (*n *= 202) and the number of clinicians (clusters) involved in this research (*n *= 12). Based on these assumptions, 220 participants will need to be recruited.

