### Primary Outcome

Our primary outcome is the number of minutes of moderate-and strenuous physical activity per week as measured by an adapted version of the Leisure Time Exercise Questionnaire [32]. In this questionnaire, participants are asked to report the average weekly frequency and duration with which they engaged in strenuous, moderate, and light exercise over the past month. Consistent with a change made to the questionnaire in a study of colorectal cancer survivors [33], participants were asked to report the average duration of time they spent exercising at each intensity, in addition to the frequency. In addition, some of the physical activities were deleted from the instrument, because they were not common activities in Australia (e.g., horseshoes, snowmobiling). The validity and reliability of the Leisure Time Exercise Questionnaire compares favourably with other physical activity questionnaires [34].

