**Figure 2 F2:**
[figure not shown]
**Recruitment and data collection procedures**.

Data collection for all measures and for participants in both conditions will occur at baseline and 12 weeks (on completion of the intervention). Participants in the intervention condition will be referred to the exercise program, whereas those in the control condition will receive usual advice about exercise from their clinician. Data collection will continue for participants in both conditions and for all measures except those of objective physical functioning at 6 months and 12 months.

For those in the intervention group, over the 12 week physical activity period, three morning and three afternoon sessions between Monday and Friday will be available for participants to attend. On commencement of the program, the project manager will provide a timetable of sessions that is convenient to the participant. The exercise physiologist will contact the participant 24 hours prior to their first physical activity session each week and remind them of their session times for the week. If the participant cannot be contacted, the exercise physiologist will contact the participant the day of their physical activity session to remind them of their session time. After two failed telephone attempts and if the participant does not attend the session, the participant will be declared 'absent' for the session. The total number of sessions attended by the participants will be recorded.

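### The 6- and 12-month ANCOVAs are available-case analyses labelled intention-to-treat; they leave out the 12-week values of men who later stop responding and can be biased if dropout depends on activity differently by arm

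*Protocol article*

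**What the plan says.** The primary aim (Study aims and hypotheses) concerns "improving the physical activity levels of prostate cancer survivors at three post-intervention time points:12 weeks, 6 months, 12 months". The Analysis section turns this into three tests. For the first, "we will perform an analysis of covariance (ANCOVA) on the post-intervention (12-week) physical activity levels of the participants in the two conditions", with the baseline score as covariate. For sustainability, "we will perform two ANCOVA on post-intervention (6 and 12 months, respectively) physical activity levels of the participants in the two conditions", again with baseline as the only covariate named.

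The analysis set is fixed in the last sentence of that section: "we will employ the intention-to-treat principle for all participants with available data at post intervention and follow-up".

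Three other statements bear on the point:

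- The primary outcome is self-reported: "participants are asked to report the average weekly frequency and duration with which they engaged in strenuous, moderate, and light exercise over the past month" (Primary Outcome). A man who does not return the questionnaire has no value.
- All measures are collected in both arms at baseline and 12 weeks, and all except objective physical functioning again at 6 and 12 months (Procedures, text after Figure 2).
- The only attrition assumption is "the attrition rate will be 10% at 12 weeks" (Participants). No figure is given for 6 or 12 months.

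The only imputation described is for accelerometer non-wear time (Accelerometer Measures). It does not cover the questionnaire.

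**The concern.** An ANCOVA at 12 months on responders, adjusted for baseline, is unbiased if non-response is unrelated to 12-month activity once arm and baseline are known. It makes no use of what a non-responder reported at 12 weeks. If men who were less active at 12 weeks are less likely to answer later, and this tendency differs between arms, the responders in the two arms are selected differently and the contrast shifts.

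Differential dropout is plausible here. The scripts in Procedures tell patients which condition they are in, and only the intervention arm has a program to abandon. At stake are two of the three tests of the primary aim, which carry the Design section's claim of sustained behaviour change. The quality of life, anxiety and depression comparisons at 6 and 12 months are exposed too, because the Analysis section gives them the same strategy.

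The label matters as well. Intention-to-treat suggests that everyone enrolled contributes, whereas the stated set is limited to those with data.

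**Working it through.** **1. The text.** Analysis set: participants with available data. Model: one per visit. Covariate: baseline. Each is stated, so none is a detail awaiting a later document. Even on the generous reading, where each visit's ANCOVA uses everyone with data at that visit, the 12-week value of a later non-responder enters neither late model.

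**2. Size.** The plan has no figure of its own to reproduce. The inputs below are assumptions, except .484, which is the effect size in Participants:

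- true late effect .30 SD; 12-week effect .484 SD
- correlation of each follow-up with baseline .5
- residual correlation r between 12 weeks and the late visit .6
- late dropout 10%, 20% or 30%; all men observed at 12 weeks
- logit P(dropout) = c − 1 × activity in SD, where dropout depends on activity; random otherwise
- normal outcomes, no clustering, 1,000,000 men per arm, so the figures show bias and not chance

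Planned estimate: coefficient of arm in late activity = arm + baseline, among responders. Comparator: missing late values predicted within arm from baseline and 12-week activity, then the same ANCOVA on everyone. This stands in for a likelihood-based repeated-measures model.

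| Dropout depends on | Planned ANCOVA at 10 / 20 / 30% | Using 12-week values |
|---|---|---|
| 12-week activity, intervention arm only | .34 / .38 / .41 | .30 throughout |
| 12-week activity, controls only | .26 / .22 / .19 | .30 throughout |
| 12-week activity, both arms, half the slope in controls | .32 / .34 / .35 | .30 throughout |
| 12-week activity, both arms, same slope and same dropout rate | .30 / .30 / .30 | .30 throughout |
| 12-week activity, one common rule on absolute activity in both arms | .28 / .27 / .27 | .30 throughout |
| unseen late activity, intervention arm only | .37 / .43 / .49 | .34 / .39 / .43 |

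Simulation and rounding error is about .01 or less. Dropout that depends on baseline alone gave bias of about zero.

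**3. Reading the table.** In the first row the overstatement is .04 to .11 SD, or .04/.30 = 13% to .11/.30 = 37% of the true effect. If the SD of 126.6 minutes in Participants applied, that is .04 × 126.6 = 5 to .11 × 126.6 = 14 minutes a week, on a true effect of .30 × 126.6 = 38 minutes.

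**4. Why it behaves this way.** The bias is approximately r × (mean 12-week residual in intervention responders − the same in control responders). It is zero when both arms are selected alike and changes sign when the selection moves to the other arm. It also scales with r: at r = .3 the first row becomes .32 / .34 / .36, about half the excess.

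**5. Limit of the 12-week data.** In the last row, using them leaves (.39 − .30)/(.43 − .30) = .09/.13, about two-thirds, of the bias at 20% dropout.

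**The case against.** A reader might infer that the late effects are biased whenever men who stop exercising also stop responding, and that the bias favours the intervention. The documents support neither. Equal dependence in both arms gives little or no bias, and dependence in controls reverses the sign. Nothing in the article says which arm will lose its inactive men. Supervised sessions end at 12 weeks, late follow-up is collected in the same way in both arms, and controls who have been told they are not in the exercise group may be the ones to disengage.

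Nor can it be said as fact that late attrition exceeds 10%. That is plausible, but the article gives no later figure.

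It is also fair to say that the .30 in the upper rows follows from the set-up: dropout was made to depend on a value that the comparator then uses. Where dropout follows unseen late activity, most of the bias remains. Men with no follow-up at all are not recovered. The 12-week comparison, on which Participants bases the sample size, gains little, because no earlier follow-up exists.

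The lack of a sensitivity analysis is not a defect of the article, since that is commonly left to a fuller document.

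All of this stands, and it limits the claim about size and direction. It does not touch the textual point: the stated rule discards 12-week values already collected and rests on a stronger missing-data assumption than a joint model would.

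**Conclusion.** The point holds in conditional form. The 6- and 12-month ANCOVAs are available-case analyses under an intention-to-treat label. They can be biased if dropout depends on post-baseline activity differently by arm. Under the assumptions listed, 10-30% dropout moves a true .30 SD to about .34-.41 when the dependence is in the intervention arm only, and to about .19-.26 when it is in controls only. With equal dependence it stays at .30 or falls slightly, to about .27-.28.

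Attrition after 12 weeks, the correlations and the direction are assumed and do not come from the documents. The point concerns mainly the two sustainability tests and the matching late secondary comparisons. It is a change the sponsor should make, not a fault that invalidates the trial.

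**What to change.** Replace the three ANCOVAs with one linear mixed model for the 12-week, 6-month and 12-month outcomes. Include arm-by-time and baseline-by-time terms, within-person correlation over visits and a clinician effect, and read the three contrasts from it. The clinician effect also meets the Design section's own statement that clustering must be taken into account.

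Define the set as every enrolled participant with at least one follow-up, analysed by his clinician's allocation. The text should not speak of randomised men, because clinicians are randomised and patients consent afterwards. Describe the present ANCOVAs as available-case if they are kept as supporting analyses, and use the same model for the late quality of life, anxiety and depression outcomes.

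A delta-type sensitivity analysis, shifting the missing late values by a stated amount separately by arm, is a useful addition for dropout that observed values do not explain.

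The cost is slightly more analysis work and some rewording. No extra data, visits or participants are needed.
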